# Effectiveness of magnetic seizure therapy versus electroconvulsive therapy for major depressive episode in China: protocol for a double-blind, randomized, non-inferiority trial

**DOI:** 10.3389/fpsyt.2025.1657906

**Published:** 2025-10-23

**Keywords:** seizure treatment, electroconvulsive therapy, magnetic seizure therapy, randomized controlled trial, major depressive disorder

## Abstract

**Clinical trial registration:**

ClinicalTrials.gov, identifier NCT06409325.

## Introduction

Electroconvulsive therapy (ECT), introduced in 1938, has long been a cornerstone treatment for mood disorders, notably Major Depressive Disorder (MDD) and treatment-resistant depression (1). Administered under anesthesia, ECT involves delivering controlled electrical currents to the scalp to induce a therapeutic seizure. Despite its efficacy, with remission rates ranging from 50% to 70% (2), ECT is underutilized due to various factors including fear, stigma, and concerns about cognitive side effects, such as short-term amnesia (3).

In pursuit of alternative treatments with comparable efficacy but fewer side effects, researchers have explored technique such as magnetic seizure therapy (MST). The first documented use of MST in humans (4) followed closely after its initial application in animal studies (5). Subsequent clinical trials have primarily focused on assessing the feasibility, efficacy, and safety of MST as a treatment for depression. Lisanby and colleagues provided early evidence supporting the feasibility of MST for depression and reported no serious adverse events associated with its use (6). Kayser and colleagues observed antidepressant effects of MST comparable to those of ECT (7). Fitzgerald and colleagues further asserted the antidepressant effects of MST, noting a lack of apparent cognitive adverse effects (8).

### Comparative action mechanisms of ECT vs. MST

Both ECT and MST utilize the induction of a seizure to achieve therapeutic effects. However, they differ significantly in the methods through which this seizure is induced and the resulting neurobiological impact (9). ECT achieves seizure induction through high-frequency, repetitive transcranial electrical stimulation. In contrast, MST employs high-frequency, repetitive transcranial magnetic stimulation. This distinction is critical as the method of stimulation impacts the nature and spread of the induced seizure. With MST, a rapid, high-intensity, time-varying magnetic field is applied to the brain, bypassing resistance and allowing for targeted stimulation of specific neurons based on the geometry of the stimulating magnetic coil. Unlike ECT, the magnetic field in MST is not impeded by non-conducting material, such as the skull, resulting in more focal brain activation (10, 11). A computational study by Deng et al. (12). compared the electric field induced by ECT and MST paradigms. They found that ECT induced a maximum electric field in the brain of 2.1–2.5 V/cm, while MST induced a field of 1.1–2.2 V/cm. This corresponds to 6.2–7.2 times and 1.2–2.3 times the neural activation threshold, respectively. Notably, the electric field induced by MST is more confined to the superficial cortex compared to ECT. The volume of the brain stimulated is significantly higher with ECT (up to 100%) compared to MST (up to 8.2%). Among MST techniques, the double cone coil exhibits the most focal stimulation, whereas bilateral ECT is the least focal. Specifically, compared to right unilateral ultra-brief pulse ECT, the electric field induced by MST is 5–10 times more focal (12, 13). While both ECT and MST achieve therapeutic effects through seizure induction, their distinct mechanisms of action result in differences in spatial specificity and depth of stimulation. MST, with its more focal and targeted approach, offers a promising alternative to ECT with potentially fewer side effects and greater therapeutic precision.

### Comparative efficacy of ECT vs. MST

Previous head-to-head studies comparing the antidepressant efficacy of ECT and MST have generally found comparable treatment outcomes (14). However, recent research has provided further insights into the effectiveness of these therapies through controlled clinical trials and systematic reviews. A double-blinded, randomized clinical trial conducted by Deng et al. (15). compared the antidepressant effects of MST, applied at 100 Hz for 10 seconds at 100% of the maximum device power, with ultrabrief pulse right unilateral ECT, applied at 6 times seizure threshold. Both MST and ECT demonstrated clinically meaningful antidepressant effects, with similar response and remission rates observed in both treatment groups. Additionally, an open-label study by Daskalakis et al. (16). evaluated the efficacy of MST at different frequencies (i.e., high-frequency MST at 100 Hz, medium-frequency MST at 60 or 50 Hz, and low-frequency MST at 25 Hz) using 100% stimulator output. Among patients with MDD, high-frequency MST produced the highest remission rate, indicating its potential as an effective treatment option. In a study by Kayser et al. (7), twenty patients with treatment-resistant depression were randomly assigned to receive either MST or ECT. The study found that both treatments produced a statistically significant and similar improvement in depressive symptoms, as measured by a 50% reduction in Montgomery Åsberg Depression Scale ratings. Several systematic reviews have also examined the comparative efficacy of MST versus ECT for depression treatment. Cai et al. (17). summarized four randomized controlled trials (RCTs) and found no significant differences in response, remission, or improvement in depressive symptoms between MST and ECT. Similarly, a meta-analysis by Chen et al. (18). included data from 10 studies comprising a total of 285 patients. The analysis revealed no significant difference in the antidepressant effect between MST and ECT, further supporting the equivalence of these treatments in depression management.

### Comparative side-effect of ECT vs. MST

The comparison of cognitive side effects between ECT and MST in the treatment of MDD has yielded varying conclusions. However, the majority of studies suggest that MST results in fewer physical side effects and no cognitive impairments compared to ECT. In a RCT by Deng et al. (15), patients receiving ECT reported higher severity of headache, nausea, and muscle pain compared to those receiving MST. Furthermore, patients receiving ECT experienced greater confusion or disorientation, and took significantly longer to regain orientation compared to MST (19). Autobiographical recall is linked to temporal cortices, notably the hippocampus. This suggests that ECT may exert a more detrimental effect on the hippocampus compared to MST. This supports the cognitive safety of MST, as evidenced by negligible cognitive adverse effects and superior performance in autobiographical memory recall. A systematic review (20) focusing on the cognitive effects of MST found little to no adverse cognitive effects. While some RCTs comparing MST and ECT reported inconsistent results regarding cognitive effects, the accumulated evidence indicates that MST has fewer adverse cognitive effects compared to ECT (17). A pilot study by Fitzgerald et al. (21) compared the cognitive effects of 100 Hz MST and ECT in patients with persistent depression. Significant improvements in psychomotor speed, verbal memory, and cognitive inhibition were observed following MST, with no reductions in cognitive performance. Conversely, ECT resulted in significant improvement in only one cognitive inhibition task. Furthermore, the MST group showed significantly greater improvement in psychomotor speed compared to ECT. In an open-label study by Kayser et al. (7), MST was investigated as an add-on therapy to controlled pharmacotherapy for treatment-resistant depression (TRD). No cognitive side effects were observed in either group, suggesting the cognitive safety of MST. Polster et al. (22) aimed to broaden insight into the side effect profile of MST compared to ECT by examining the disruption of acute verbal memory processes after treatment. Overall, evidence from clinical trials and systematic reviews suggests that MST is associated with fewer physical side effects and superior cognitive safety compared to ECT in the treatment of MDD.

### Biomarker rationale

Neurophysiological biomarkers offer a unique opportunity to tailor seizure therapies to individual patients. For instance, EEG can capture real-time seizure characteristics and brain connectivity, while ECG HRV reflects autonomic nervous system dynamics-both of which are disrupted in MDD and modulated by MST/ECT (23, 24). By linking these biomarkers to treatment outcomes, we aim to establish a data-driven framework for personalized therapy, addressing the heterogeneity of MDD and optimizing treatment selection. This approach builds on prior work showing that MST’s focal stimulation elicits distinct EEG signatures compared to ECT (25), and that HRV abnormalities predict treatment response and side effects.

### Study objectives

Despite advancements in MST and ECT for MDD, there remains a need for further research to replicate clinical outcomes and understand the therapeutic targets of these treatments. This project titled “Chinese Union: Replication, Efficacy, and Safety of Seizure Therapy with Evaluation-based Precision (CURES-STEP)” phase I initiated by the [removed for peer review], aims to address these gaps through a double-blinded, randomized, non-inferiority investigation comparing the efficacy, tolerability, cognitive adverse effects, and neurophysiological biomarkers of MST and bilateral ECT in patients with MDD. The primary objectives of the study are twofold: 1. To replicate the comparable antidepressant efficacy and reduced side effects (with HVLT-R as an additional primary outcome) observed in previous comparisons between MST and ECT. 2. To utilize electroencephalography (EEG) (25) and electrocardiography (ECG) (23) markers as neurophysiological biomarkers to assist in treatment decision-making between ECT and MST, and to predict treatment outcomes including antidepressant effects and cognitive side effects. We believe that MST and ECT are not simply interchangeable treatments, and that leveraging neurophysiological characteristics may help tailor treatment decisions for individual patients with MDD. By examining both clinical outcomes and neurophysiological biomarkers, we aim to provide valuable insights into the efficacy, safety, and personalized treatment approaches for MDD using seizure therapies. Additionally, this study aims to validate the clinical application value of a domestically developed MST device approved by the National Medical Products Administration (NMPA) in China, as previous MST studies utilized the MagPro MST (MagVenture A/S, Denmark) device (26, 27).

## Methods

### Study settings

This multicenter trial will be conducted at seven clinical center: Shanghai Mental Health Center (SMHC), First Hospital of Shanxi Medical University, The Affiliated Brain Hospital of Guangzhou Medical University, The First Hospital of Hebei Medical University, Shenzhen Kangning Hospital, Ningbo Kangning Hospital, The Fourth People’s Hospital of Wuhu. All interventions and assessments will take place in the neuromodulation department of these hospitals. EEG and ECG acquisitions will be conducted in the electrophysiology department within the same clinical institution. The trial was commenced from December 1, 2024 and conclude on December 30, 2027. The authors assert that all procedures contributing to this work comply with the ethical standards of the relevant national and institutional committees on human experimentation and with the Helsinki Declaration of 1975, as revised in 2013. All procedures involving human subjects/patients were approved by the Ethics Committee of SMHC (Approval No. 2025-21) and registered on the clinical trials website prior to the commencement of enrollment (NCT06409325, ClinicalTrials.gov).

### Study design

The present clinical protocol is designed as a double-blind, parallel, non-inferiority, randomized clinical trial.

### Study summary

**Figure 1** provides an overview of the study flow. Participants will be randomly allocated to either the ECT or MST group. Each center aims to recruit 15 participants for each group (ECT and MST), using block randomization, resulting in a total of 30 participants per center (15 per group). Across seven centers, this will yield a total sample size of 210 participants (105 per group). The trial comprises a 12-session intervention phase of ECT/MST, spanning approximately 4 weeks, followed by a 12-week observation period. For the first three treatment sessions, participants will receive consecutive sessions. Subsequently, there will be a one-day interval between sessions 4 to 6, a two-day interval between sessions 7 to 9, and a three-day interval between sessions 10 to 12, ensuring completion within a month. Following treatment completion, participants will undergo follow-up clinical observations every four weeks for 12 weeks. EEG and ECG recordings will be obtained at baseline, post-session 3, 6, 9, 12 (3 hours after each session), and at the 12-week follow-up. All evaluations will be conducted under standardized conditions throughout the sessions. **Table 1** delineates the time points for clinical assessments, interventions, and electrophysiological examinations.

**Figure 1 f1:**
[figure not shown]
Flow diagram of the study design. This flowchart outlines the trial design comparing electroconvulsive therapy (ECT) and magnetic seizure therapy (MST) in patients with major depressive disorder (MDD). A total of 210 MDD participants (recruited from 7 centers, 30 per center) undergo screening and enrollment with informed consent. At baseline (Day 0), demographic/clinical assessments and electrophysiological measurements (EEG/ECG) are conducted. Participants are then randomized via blocked randomization to either the ECT group (n=105) or MST group (n=105). Treatment sessions are delivered in four phases: Days 1–3 (sessions 1–3, daily), Days 4–9 (sessions 4–6, every 2 days), Days 10–18 (sessions 7–9, every 3 days), and Days 19–30 (sessions 10–12, every 4 days). Clinical/cognitive assessments and EEG/ECG measurements are performed after every 3 sessions (end of each phase). A 12-week post-intervention follow-up includes clinical/cognitive assessments every 4 weeks, with additional EEG/ECG measurements at week 12.

**Table 1 T1:** Schematic summary and milestones for enrolment, ECT/MST treatment, and assessments across the study time-line.

Time-point	Eligibility screen	Informed consent	Allocation	Intervention (ECT/MST)	Assessments			
					Demographic features	Clinical /Cognitive performances	EEG	ECG
Day 0	X	X	X		X	X	X	X
Treatment phase								
Day 1				X				
Day 2				X				
Day 3				X		X	X	X
Day 5				X				
Day 7				X				
Day 9				X		X	X	X
Day 12				X				
Day 15				X				
Day 18				X		X	X	X
Day 22				X				
Day 26				X				
Day 30				X		X	X	X
Post-treatment phase								
Week 4						X		
Week 8						X		
Week 12						X	X	X

### Participants and recruitment

The recruitment process will target patients from seven participating centers. Eligibility assessment will exclusively involve individuals receiving clinical services at these facilities. Initial screening of potential participants meeting the eligibility criteria will be conducted by two experienced licensed psychiatrists at each center, each with a minimum of five years of clinical experience. Upon confirming eligibility, detailed information about the protocol will be provided to the participants and their legal guardians. Both participants and their legal guardians must sign a consent form indicating their willingness to participate in the study before official enrollment.

### Inclusion criteria

Participants must meet the diagnostic criteria for MDD as outlined in the Diagnostic and Statistical Manual of Mental Disorders, Fifth Edition (DSM-5).Participants must have a baseline score of 18 or higher on the 24-item Hamilton Depression Rating Scale (HDRS-24) (28).All patients are MST/ECT naïve and are required to be considered suitable for a course of ECT by both their treating psychiatrist and the study psychiatrist.During the trial’s treatment period, participants must be using a single antidepressant medication at a stable dose.Participants must be between the ages of 18 and 65 years.Informed consent from both parents and legal guardians is required.

### Exclusion criteria

Individuals with current or history of organic brain disorders or neurological disorders will be excluded from the study.Participants with a Wechsler Abbreviated Scale of Intelligence (WASI) score of less than 70 will be excluded.Presence of contraindications to anesthesia, such as: allergic reactions to anesthesia medications.Individuals currently taking antiepileptic drugs, benzodiazepines, or other medications that may affect seizure activity will be excluded from the study.Those with exposure to ECT, modified ECT, MST, transcranial magnetic stimulation (TMS), transcranial direct current stimulation (tDCS), transcranial alternating current stimulation (tACS), or other neurostimulation treatments in last 6 months will be excluded.Individuals with cochlear implants, cardiac pacemakers, implanted devices, or metal in the brain will be excluded from participation.Pregnant or lactating individuals will be excluded from the study.Individuals currently participating in another concurrent clinical trial will not be eligible for inclusion.Participants who refuse to provide informed consent to participate in the trial will be excluded.Other circumstances deemed unsuitable for participation by researchers will result in exclusion.

### Sample size estimation

The sample size calculation for this study was conducted through *a priori* power analysis using G*Power 3.1.9.7 (29). Parameters were chosen, including α = 0.05 and power (1-ß) = 0.95. An effect size of f = 0.1 was selected based on previous research findings (15). Specifically, in the intent-to-treat sample (N = 73), 18 participants (51.4%) in the MST group (N = 35) and 16 (42.1%) in the ECT group (N = 38) met response criteria, while 13 (37.1%) in the MST group and 10 (26.3%) in the ECT group met remission criteria. In addition to the two experimental conditions (MST and ECT), covariates including age, sex, duration of illness, age of onset, intelligence quotient (IQ), and antidepressant usage were considered, resulting in a total of 6 covariates. Accounting for a potential dropout rate of 20%, the final estimated number of participants required for the study was determined to be 210. (**Figure 2**).

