**Figure 2 f2:**
[figure not shown]
G*Power-based sample size calculation for a repeated-measures ANOVA with a within-between interaction. The plot depicts an *a priori* power analysis to determine the required sample size for a repeated-measures analysis of variance examining the interaction between a between-subjects factor (2 groups) and a within-subjects factor (6 measurement time points). The upper panel shows the central F-distribution under the null hypothesis (red solid curve) and the noncentral F-distribution under the alternative hypothesis (blue dashed curve). The critical F-value (2.22502) is indicated by the green vertical line. The red shaded region represents the α error probability (Type I error, set at 0.05), and the blue shaded region denotes the β error probability (Type II error), with power (1−β) targeted at 0.95. Input parameters include: effect size (f) = 0.1, α = 0.05, number of groups = 2, number of repeated measurements = 6, correlation among repeated measures = 0.5, and sphericity correction (ϵ) = 1. Output parameters reveal a total required sample size of 166, a noncentrality parameter (λ) of 19.92, numerator degrees of freedom (df) = 5, denominator df = 820, and an actual power of ~0.95.

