### Outcomes

#### Primary outcome

The primary outcome measure is the change in HDRS-24 total score from baseline to the 12-week follow-up, which is assessed after the completion of the 12-session acute treatment phase (conducted over 4 weeks) and a subsequent 12-week post-treatment observation period. A reduction of at least 50% in the HDRS-24 score indicated a response to treatment, while a reduction of at least 60% in the HDRS-24 score and a total score of 8 or less indicated remission. Change in HVLT-R total recall score from baseline to the 12-week follow-up (assessing verbal memory, a key cognitive domain sensitive to seizure therapy effects).

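### The response and remission rates quoted in support of f = 0.1 do not support it as a six-visit time-by-group interaction effect, so the stated 95% power does not follow from its stated basis

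*Protocol article*

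**What the plan says.** The section on sample size estimation in the protocol article sets the error rates ("Parameters were chosen, including α = 0.05 and power (1-ß) = 0.95") and then the effect: "An effect size of f = 0.1 was selected based on previous research findings (15". The next sentence makes the basis specific and reports only binary outcomes by arm: "18 participants (51.4%) in the MST group (N = 35) and 16 (42.1%) in the ECT group (N = 38) met response criteria", and "13 (37.1%) in the MST group and 10 (26.3%) in the ECT group met remission criteria". It gives no HDRS mean, SD, time course or interaction effect.

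The Figure 2 legend describes a "sample size calculation for a repeated-measures ANOVA with a within-between interaction". It lists the settings: "Input parameters include: effect size (f) = 0.1, α = 0.05, number of groups = 2, number of repeated measurements = 6", with correlation 0.5 and sphericity correction 1. The output is N = 166, λ = 19.92, degrees of freedom 5 and 820, and power of about 0.95. With 20% dropout the section arrives at 210.

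Under the primary outcome heading, the endpoint is a score: "The primary outcome measure is the change in HDRS-24 total score from baseline to the 12-week follow-up".

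**The concern.** The symbol f means different things in different tests. A between-group f at one time point measures how far apart two arms are. A within-between interaction f measures how much that gap changes across visits. Two pairs of percentages observed in two arms speak to the first kind, whereas Figure 2 uses the second. The article shows no step from one to the other, nor from percentages to an HDRS-24 score.

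The 95% power and the 166 evaluable patients are presented as resting on the cited trial. If that support is missing, a reader could give a non-significant interaction more weight as evidence of similarity than the design can bear.

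**Working it through.** **Inputs.** From the sample-size section: response 18/35 and 16/38, remission 13/35 and 10/38, dropout 20%. From Figure 2: 2 groups, m = 6, ρ = 0.5, ε = 1, α = 0.05, N = 166.

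**1. Reproduce Figure 2.** λ = f² × N × m × ε/(1 − ρ) = 0.1² × 166 × 6/0.5 = 19.92. The degrees of freedom are (2 − 1)(6 − 1) = 5 and (166 − 2)(6 − 1) = 820. The critical F is 2.22502 and the power is 0.950. All agree with the legend. For dropout, 166/0.8 = 207.5, so 210 (7 × 30) is consistent. The printed λ also fixes the definition of f in use: λ = 12 × f² × N.

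**2. What an interaction f of 0.1 requires.** Let δ_t be the arm difference at visit t in SD units. Then f = √[mean over visits of ((δ_t − mean δ)/2)²]. Suppose δ_t always lies between 0 and d.
- The largest possible f occurs with three visits at 0 and three at d: f = d/4. So f = 0.1 needs d = 0.40.
- If the difference is 0 at baseline and d at all five later visits: f = d × √5/12 = 0.186d. So f = 0.1 needs d = 0.1/0.186 = 0.54.

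**3. What the quoted rates correspond to.** Three usual conversions to a standardised difference are:
- arcsine: h = 2·arcsin√p₁ − 2·arcsin√p₂
- logit: d = ln(OR) × √3/π
- probit: d = Φ⁻¹(p₁) − Φ⁻¹(p₂)

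Power is from the noncentral F with 5 and 820 degrees of freedom and λ = 12 × f² × 166.

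| Rate, conversion | d | d/2 (between-arm f) | d/4 (largest interaction f) | Power, most favourable profile | Power, constant after baseline |
|---|---|---|---|---|---|
| Response, arcsine | 0.187 | 0.094 | 0.047 | 32% | 18% |
| Response, logit | 0.207 | 0.104 | 0.052 | 38% | 22% |
| Response, probit | 0.235 | 0.118 | 0.059 | 49% | 28% |
| Remission, arcsine | 0.233 | 0.117 | 0.058 | 48% | 27% |
| Remission, logit | 0.278 | 0.139 | 0.069 | 65% | 38% |
| Remission, probit | 0.306 | 0.153 | 0.076 | 75% | 46% |

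Worked example, first row: λ = 12 × 0.0468² × 166 = 4.36, which gives power 0.315.

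With all 210 patients evaluable, the most favourable profile gives 40–86%.

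**4. Sampling error in the rates.** On the arcsine scale the standard error is √(1/35 + 1/38) = 0.234, so the 95% half-width is 1.96 × 0.234 = 0.459. The intervals for h are −0.27 to 0.65 for response and −0.23 to 0.69 for remission. Both contain 0.40 and 0.54. At either upper limit Figure 2's calculation exceeds 99% power under both profiles.

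**The case against.** Five objections deserve an answer.

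- **Origin of 0.1.** A reader might infer that f = 0.1 was calculated from the rates, since half of h is 0.094 and 0.117. The article prints no such step, the other conversions give 0.104 to 0.153, and the cited trial may report scores that informed the choice. The documents therefore support only the narrower statement that the rates shown do not justify an interaction f of 0.1.
- **A ceiling on power.** A reader might also infer that the cited evidence caps power at 75%. It does not. The range uses point estimates from 35 and 38 patients, and the intervals in step 4 are wide enough to include effects with very high power. A difference that reversed direction over time could also exceed d/4, although nothing cited suggests one.
- **Conversion.** Response is a percentage-reduction threshold and remission is a stricter threshold criterion. A latent d from either only approximates an HDRS-24 difference at a visit. This weakens the exact figures, but it also strengthens the point that such rates are a poor basis for this input.
- **Relevance.** The title and the study design section describe a non-inferiority trial, and the analysis section plans a model with three time points, not six. The figures in step 3 are power to detect a difference with an unplanned test, and the cited rates favour MST. This stands, and it determines the remedy.
- **Convention.** f = 0.1 could simply be a conventional small effect. If so, the article should say that instead of attributing it to earlier findings.

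**Conclusion.** The point holds as a failure of justification. The software calculation is right; its effect-size input is not supported by the rates offered for it. In Figure 2's terms, f = 0.1 means a change in the arm difference of at least 0.40 SD (0.54 SD if constant after baseline), against roughly 0.19–0.31 SD from the point estimates of the rates. Taking those estimates as true, the same calculation at N = 166 gives about 32–75% at best and 18–46% for a constant post-baseline difference.

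These percentages assume no baseline difference, a one-directional difference never above d, Figure 2's correlation and sphericity, and a latent-scale conversion. They show the size of the gap between evidence and input. It would be wrong to read them as the trial's power, or to conclude that 210 patients are too few: neither follows, because they do not address the non-inferiority comparison.

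**What to change.** Keep N = 210 and make three changes to the text.

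1. Delete the statement that f = 0.1 rests on the cited response and remission rates. Alternatively, label it a convention and state that it implies a change of 0.40–0.54 SD in the arm difference, depending on the time profile.
2. Replace the 95% claim with the power or precision that about 168 evaluable patients (210 × 0.8) give for the planned Week 12 HDRS-24 non-inferiority comparison. State the margin, the assumed true difference and the SD of change, all in HDRS-24 points.
3. Do not print 18–75% as the trial's power.

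The cost is a rewritten sample-size paragraph and Figure 2 legend, and a stated power that is likely to be less favourable. No patients, visits or procedures are added.
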